# **APPENDIX G – INSTRUCTIONS LABEL FOR PARTICIPANT**

**Control group:**

| **CRO-2022-04-FLU-REG-BZ-ZM**  **Product XXX**  *Brush your teeth’s twice a day (in the morning and at night) for two minutes*  *Do not ingest.*  *Restrict use for the participants of this research.*  *Only adults. Keep out of touch of children’s.*  *In emergency case, please contact* ***[name] – (Telephone number omitted for privacy purposes)*** |
| --- |

**Test group:**

| **CRO-2022-04-FLU-REG-BZ-ZM**  **Product XXX**  *Brush your teeth’s twice a day (in the morning and at night) for two minutes.*  *After toothbrushing, gargle your mouth with 20ml of mouthwash for 30 seconds, twice a day.*  *Do not ingest.*  *Restrict use for the participants of this research.*  *Only adults. Keep out of touch of children’s.*  *In na emergency case, please contact:*  ***[name] – (Telephone number omitted for privacy purposes)*** |
| --- |

# **APPENDIX H – VISIT FORM**

Participant number: Date: __/__/__

Is the patient currently taking any medication? (including over-the-counter products)

( ) Yes No ( )

In affirmative case, list all medications:

| **Medication** | **Total daily dose** | **Start date** | **End date (circle the “C” in case of a medication for continuous use** | **Indication** |
| --- | --- | --- | --- | --- |
|  |  |  | **C** |  |
|  |  |  | **C** |  |
|  |  |  | **C** |  |
|  |  |  | **C** |  |

All medications must be reviewed by the study supervisor.

1. Have there been any unexpected or serious reactions since the previous exam? ( ) Yes No ( )

2. For the condition mentioned above, was there any treatment prescribed? ( ) Yes No ( ) ; If yes, please describe: ______________________________________________________________________

3. Has any dental treatment been performed since the previous examination? ( ) Yes No ( );

If yes, please describe: ______________________________________________________________________

4. Since the last exam, have any medications been prescribed? ( ) Yes No ( );

If yes, describe dose, duration and reason: ______________________________________________________________________

5. Is the volunteer pregnant or breastfeeding? ( ) N/A ( ) Yes ( ) No

6. Do any of the answers to questions 1 to 5 justify the exclusion of the participant's data from the statistical analysis? ( ) Yes No ( );

If yes, please explain: ______________________________________________________________________

7. Will the participant continue in the study? ( ) Yes No ( )

If the answer to question 7 is “No”, complete question 8.

8. Did the participant complete the entire study? ( ) Yes No ( )

If not, please explain: ____________________________________________________________________________________________________________________________________________

Date: ______ Signature of the examining dentist: ______________________________

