### Sample size

The sample size of 150 individuals (75 per group) was based on internal data from the sponsor of this study. It was determined that 60 individuals per group are needed for 80% power for the occurrence of flu-like symptoms. Considering the nature of the study and the demand for daily questionnaire responses, an attrition rate of 25% is assumed over the course of the study.

- - 1. Inclusion criteria

Individuals must meet all the following criteria:

1. Sign this informed consent form (ICF) (Appendix A);

2. Men or women, aged between 18 and 70;

3. Good systemic general health as determined by study investigators;

4. Availability of 90 days to participate in the study;

- - 1. Exclusion criteria

During the study, the following exclusion criteria will be considered:

1. Be participating in any other clinical study;

2. Being pregnant or breastfeeding;

3. Present a history of allergies to oral hygiene products, personal hygiene products, or their ingredients;

4. Have mouth irritation or use oral anesthetic sprays;

5. Have diabetes;

6. Be undergoing extensive dental treatment or oral surgery during the study;

7. Present immunocompromised (HIV, AIDS, immunosuppressive drug therapy);

8. Use complete dentures;

9. Have carpal tunnel syndrome or arthritis in the hands.

10. Participant who substantially fails to follow the required protocols;

11. Participant who fails to attend scheduled appointments;

12. Participant who is treated, during the study period, with medications that may interfere with the parameters being analyzed in the study;

13. Participant who is treated by a medical or dental service, and this may interfere with the parameters being analyzed in the study;

14. Participant who develops serious adverse reactions. The investigator will immediately record the information on the Adverse Reactions Form (Appendix B);

15. The participant who chooses to end their participation in the study;

16. Participant reports being pregnant during the study.

- 1. **Tests products**

Participants will be randomized into one of the following experimental regimens and will receive products as follows:

Group control:

● Colgate Maximum Cavity Protection® Toothpaste.

● Commercially available soft toothbrush.

Test Group:

● Mouthwash containing 0.075% CCP and 0.28% zinc lactate, in an alcohol-free base, commercially available in Brazil.

● Colgate Maximum Cavity Protection® Toothpaste.

● Commercially available soft toothbrush.

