### 4.4.5 Subsequent assessment

Subsequent evaluations will be performed after 30 and 90 days of use of the designated products. Participants will attend the research location to be evaluated and receive additional products, according to the group to which they were allocated. During these visits, an Oral Assessment of Soft and Hard Tissues will be carried out (Appendix D). A Visit Form (Appendix H) will be completed for all study participants.

After the 90 days of the experiment, all participants will be instructed to no longer use the products provided, returning to their normal oral hygiene habits. All unused products will be handed over to an assistant not involved in the clinical examination and will be discarded following Federal University of Pelotas waste disposal guidelines.

- 1. **Monitoring and discontinuity of participants**

All randomized research participants who receive the products will be monitored according to the following protocol:

Participants will be considered to have completed the study if they are re-evaluated at the end of 90 days. They will only be considered lost to follow-up if no contact was established during the completion of the study, and there is, therefore, insufficient information to determine the status of the research participant. Efforts will be made to determine the reasons why the participant did not return for the required visit(s) or the reasons for the participant's withdrawal from the study. Participants will exit the study if any of the following occur:

1. Participant who substantially fails to follow the required protocols;

2. Participant who fails to attend scheduled appointments;

3. Participant who is treated, during the study period, with medications that may interfere with the study parameters being analyzed;

4. Participant who is treated by a medical or dental service, and this may interfere with the parameters being analyzed in the study;

5. Participant who develops serious adverse reactions. The investigator will immediately record the information on the Adverse Reactions Form (Appendix B);

6. The participant who chooses to end their participation in the study;

7. Participant reports being pregnant during the study.

The researcher will be responsible for promptly notifying the Federal University of Pelotas Research Ethics Committee about all participants who leave the study prematurely and experience serious adverse effects.

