## **4.7. Statistical analysis**

Chi-square test will be performed for gender data, and an independent t-test for the age variable, to test the hypothesis that the groups present balanced distribution of variables. The proportion of symptom-free days (i.e., none of the 10 symptoms were present) will be used for the primary outcome variable. Chi-square test will be used to compare the proportion of symptom-free days for the experimental groups. Analysis of variance can be used to compare groups. Significance level will be set at 95%.

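### Appendix H lets a randomised participant's data be excluded from the analysis for events after randomisation, without criteria, and section 4.7 defines no all-randomised analysis to prevent it

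*Combined protocol and SAP*

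**What the plan says.** Three places in the combined protocol and SAP bear on who is analysed.

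- **Appendix H (Visit Form), question 6.** The form is completed at days 30 and 90 and signed by the examining dentist. It asks: "Do any of the answers to questions 1 to 5 justify the exclusion of the participant's data from the statistical analysis". The answer is yes or no with a free-text reason.
- **Section 4.2.3, items 10-16, and section 4.5.** The exclusion criteria include events that can only occur after entry, for example: "Participant who is treated, during the study period, with medications that may interfere with the parameters being analyzed in the study". Section 4.5 repeats these items under the words "Participants will exit the study if any of the following occur". Interfering medications are not listed, substantial non-adherence is not defined, and no number of missed appointments is given. Section 4.5 also counts anyone re-evaluated at day 90 as a completer, and says of participants: "They will only be considered lost to follow-up if no contact was established during the completion of the study".
- **Section 4.7.** The primary outcome is the proportion of symptom-free days, compared by chi-square test. No analysis population, intention-to-treat principle, rule for diary days around an exit, or sensitivity analysis is given.

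**The concern.** A randomised comparison is protected only while the analysed groups are the randomised groups. Question 6 allows that to be broken one participant at a time, on information that arises after randomisation, and section 4.7 has nothing to override it.

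The triggers are not neutral. The outcome is freedom from ten cold symptoms, so a medicine prescribed for a cold is a plausible consequence of the outcome. A reaction to the mouthwash is a consequence of the product. Control participants receive no mouthwash, so everyone knows their regimen, and care-seeking and attendance may differ by arm. Unequal exclusion of ill participants can produce a difference where none exists. Equal exclusion discards information from a trial with little to spare. Diary days not collected after an exit cannot be recovered later.

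**Working it through.** **1. The plan's own figure.** The point rests on no stated figure, but the loss allowance is relevant. Section 4.2.1 says "It was determined that 60 individuals per group are needed for 80% power for the occurrence of flu-like symptoms" and "an attrition rate of 25% is assumed over the course of the study". The stated 75 per group is 60 × 1.25. After a 25% loss, 75 × 0.75 = 56.25, about 56 per group, remain. The 60 cannot be re-derived, because no effect size, rate or SD is given. Assuming two-sided α = 0.05, it implies d = (1.960 + 0.842) × √(2/60) = 0.51 SD. Power is Φ(d√(n/2) − 1.960): 77.2% at 56 per group and 87.9% at 75. The last figure assumes that every randomised participant contributes data.

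**2. Which events reach which rule.**

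| Event after randomisation | Appendix H, question 6 (data) | Sections 4.2.3 and 4.5 (exit) |
|---|---|---|
| Reaction | Yes, unexpected or serious | Serious only |
| Treatment prescribed for it | Yes | If it may interfere |
| Dental treatment | Yes, any | If it may interfere |
| Prescribed medication | Yes, any | If it may interfere |
| Over-the-counter remedy | No (recorded above question 1) | If it may interfere |
| Medical visit as such | No | If it may interfere |
| Pregnancy | Yes | Yes |
| Missed appointments, substantial non-adherence | No | Yes |

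Only the middle column concerns deleting data.

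**3. Effect on the share ill (assumed rates).** Let p be the share with a cold and q the share of ill participants excluded. The share ill among those kept is p(1 − q)/(1 − pq), and the odds of illness are multiplied by (1 − q).

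- Equal q: the odds ratio is unchanged. With p = 40% vs 30% and q = 50%, those kept show 0.20/0.80 = 25.0% vs 0.15/0.85 = 17.6%. The absolute difference falls from 10.0 to 7.4 points, the odds ratio stays at 1.56, and the risk ratio (test/control) moves from 0.75 to 0.71.
- Unequal q, no true effect: the odds ratio (test/control) becomes (1 − q_test)/(1 − q_control). With p = 60%, q = 20% in control and 40% in test, those kept show 0.48/0.88 = 54.5% vs 0.36/0.76 = 47.4%, a spurious odds ratio of 0.60/0.80 = 0.75.

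**4. Error rate and power (simulation, 75 randomised per arm, two-sided 5% test of the share ill).**

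| True share ill, control/test | Excluded among ill, control/test | Trials rejecting |
|---|---|---|
| 60%/60% | 0/0 | 5.5% |
| 60%/60% | 30%/30% | 5.0% |
| 60%/60% | 20%/40% | 12.6% |
| 60%/60% | 40%/20% | 12.7% (opposite direction) |
| 60%/60% | 10%/50% | 36.5% |
| 60%/35% | 0/0 | 88.2% |
| 60%/35% | 30%/30% | 80.1% |
| 60%/35% | 50%/50% | 70.9% |

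**5. On the scale of the primary outcome.** Assume that ill participants have on average 10 symptom days in 90 (gamma, shape 2, scale 5, limited to 1-90) and the others none.

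- No true effect, 60% ill in both arms, 20% of ill controls and 40% of ill test participants excluded: a spurious gain of 0.8 points in symptom-free days if exclusion does not depend on the number of symptom days, and 1.5 points if it rises with them. Reversing the rates reverses the sign.
- True 60% vs 40% ill, a full difference of 0.20 × 10/90 = 2.2 points, same exclusion rule in both arms: at 30% and 50% exclusion the difference is 2.15 and 2.0 points if unrelated to symptom days, and 1.7 and 1.3 points if rising with them.

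All these figures treat an exclusion as removal of the whole participant.

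**The case against.** The strongest reply is that the text is milder than it looks, and much of this stands.

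- Question 6 permits exclusion and does not require it. It does not reach self-bought remedies, medical visits as such, or missed visits.
- Sections 4.2.3 and 4.5 end participation. Neither says that diary days already sent are discarded. A reader might infer that every exit deletes the participant; the documents do not say so.
- A reader might infer that missing the day-30 visit forces exit. That is one reading of an ambiguous rule: the same section counts anyone seen at day 90 as a completer and defines loss to follow-up by absence of contact.
- A reader might infer that reactions can occur only in the test arm. Section 5.2 accepts irritation or sensitivity with any of the products; only reactions to the mouthwash itself are confined to the test arm.
- Cold medication is never named. That interfering medication includes it is a reasonable inference for a symptom outcome, not a stated rule.
- Sections 4.4.3 and 6.2 keep the examiner blind, which limits deliberate selection by arm.

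What does not stand is the conclusion that the matter is harmless. Blinding the examiner does not remove selection through events that the outcome, the product or an unmasked participant's behaviour brings about. A discretionary rule without criteria is not made safe by being optional.

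**Conclusion.** The point holds as a gap in the analysis plan: exclusion of data is allowed case by case without criteria, the use of data before and after exit is unspecified, and no all-randomised primary analysis is stated.

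The bias is of unknown size and direction, since the documents give no rates of illness, treatment or exclusion. Every figure on bias above is an illustration. Unequal exclusion can create a false difference in either direction; equal exclusion mainly costs power and precision. A reader might go further and say that the plan generally dilutes a true effect. That is not supported: under equal exclusion the odds ratio for illness is unchanged and the risk ratio can move away from the null, while shrinkage of the absolute difference, including in symptom-free days, depends on the assumed rates and on how exclusion relates to symptom burden.

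It should be corrected because it touches the primary comparison and the remedy is cheap.

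**What to change.** 1. Delete question 6 from Appendix H.
2. State in section 4.7 that the primary analysis includes every randomised participant in the assigned arm, using all diary days reported, including those before any exit, and say how days without an entry are handled.
3. State in section 4.5 that weekly diary photographs continue to day 90 after an exit event, where the participant still consents and the participation rules allow it.
4. Keep any exclusion-based set as a sensitivity analysis only, with criteria fixed in advance and applied blind to arm.

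The exit and product rules should not be rewritten for this purpose. The sponsor should instead reconcile sections 4.2.3, 4.5, 4.6 and 7 where they pull apart: exit for interfering medication against investigator discretion over concomitant therapy; missed appointments against completion at day 90 and the loss-to-follow-up definition; and how termination of participation on pregnancy bears on diary collection.

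The cost is a few sentences and one form line. Diaries already arrive by phone under section 4.4.1, so extra follow-up is small. The downside is that the estimate includes non-adherence and may be slightly smaller.
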